**13.7 Analysis plan summary**

All randomized patients will be included in the analysis. The analysis will be performed on an intention-to-treat basis. Data from participants lost to follow-up will be censored at the last contact. To assess the success of randomization, a summary of baseline variables by study arm will be tabulated. Continuous data will be summarized with descriptive statistics, including n, mean, standard deviation, minimum, maximum, median and interquartile range. Categorical data will be summarized using counts and percents. A significance level alpha=0.05 will be used to perform significance testing and construct confidence intervals. Heterogeneously distributed variables will be regarded as potential confounders and will be adjusted for in multivariable modeling. Missing data will be summarized by treatment groups, and missing patterns will be assessed using graphical and modeling approaches and an appropriate multiple imputation technique will be applied.24 All analyses will be done using SAS version V8 (Cary, NC, U.S).

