**13.9 Efficacy analysis**

The study hypothesis is that HIV incidence will be lower among participants receiving tenofovir than among participants receiving placebo. A log-rank statistic will be used to test the efficacy of treatment.25 The efficacy of treatment will be estimated as

Efficacy = 1 – *RR*

where *RR* is the hazard ratio estimated from a discrete time proportional hazards regression model with an indicator variable representing treatment arm. Confidence intervals for efficacy can be calculated using the confidence limits for the *RR*.

All analyses will be performed on an intention-to-treat basis. Rates of HIV seroconversion with Poisson 95% exact confidence intervals will be used to summarize the data. Discrete time proportional hazards regression will be applied to adjust the treatment effect for age and gender and for other demographic or behavioral variables, which, despite the randomization, were heterogeneously distributed between the study arms.

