If the point estimate of efficacy at the interim analysis is <20%, a conditional power futility analysis29 will be carried out. If the conditional power futility analysis shows less than 10% power to demonstrate a lower 95% confidence interval of tenofovir efficacy of >10% given the observed data and using the original trial assumptions of event rates for future observations in the remaining person-years to be accrued, the DSMB will consider recommending trial termination.

The interim analysis report will include a list of AEs, missed visits, drop-outs, adherence information, protocol violations and number, percentage and rates of occurrence of primary and secondary outcomes. Frequencies and crude rates with 95% confidence intervals will be used for data summarization. If necessary, adjustment of sample size will be performed. Multivariable analysis will adjust for baseline differences between study arms.

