**14.2 Safety monitoring plan**

The Principal Investigator is responsible for continuous close monitoring of all AEs that occur among study participants, and for alerting study staff if unexpected concerns arise. The DSMB will have members from Botswana, Thailand, and the United States (sites of CDC supported tenofovir HIV prophylaxis trials). Members will be selected based on demonstrated expertise in statistics, medical ethics, epidemiology, behavioral science, medical care of HIV-infected individuals, and clinical research experience. The DSMB will be responsible for periodic (or emergency) review of safety data, and decisions about holding accrual or administration of study product for safety concerns.

Prior to initiation of the trial a data safety monitoring plan will be written and agreement about the plan reached with the DSMB. It will include at least the following:

- Specification of the adverse event detection and reporting system
- Content of interim data reports
- Frequency of interim data reviews
- Statistical methods for interim analyses
- Specification of safety and efficacy stopping rules
- Distribution of interim review reports

Interim reports will include at least the following information, by treatment arm, gender and age:

- Number randomized
- Number and timing of missed visits and drop-outs, accumulated follow-up time
- Baseline characteristics of study population
- Medication adherence
- Protocol violations, including ineligible persons enrolled, number who received an unassigned treatment, instances of unblinding
- Safety and efficacy outcomes
- number, percent, and rate of occurrence of primary outcomes
- number, percent, and rate of occurrence of secondary outcomes
- line listing of adverse events

Interim reports will also include:

- Multivariate analyses of outcomes adjusted for baseline differences between arms/strata
- Analyses of efficacy outcomes adjusted for medication adherence

At predetermined review intervals, the board will be convened (in person or by phone) to review the data provided and make a recommendation about:

- - Whether sufficient safety is demonstrated in the phase II trial to proceed to phase III
  - Whether safety and efficacy interim data indicate the continuation, revision, or discontinuation of the phase III trial

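### Beyond age and gender, covariates enter the adjusted efficacy model because they differ between arms, not because they predict HIV infection

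*Protocol*

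**What the plan says.** Four places in the protocol tie adjustment to observed differences between the arms.

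- **13.7**, for analyses in general: "Heterogeneously distributed variables will be regarded as potential confounders and will be adjusted for in multivariable modeling".
- **13.9**, for the efficacy model: the treatment effect is adjusted "for age and gender and for other demographic or behavioral variables, which, despite the randomization, were heterogeneously distributed between the study arms". Age and gender are therefore always in; the rest are conditional.
- **13.10**, at the interim: "Multivariable analysis will adjust for baseline differences between study arms".
- **14.2**, in the interim reports to the DSMB: "Multivariate analyses of outcomes adjusted for baseline differences between arms/strata".

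The main efficacy analysis is described separately in 13.9 and without covariates: "A log-rank statistic will be used to test the efficacy of treatment", and efficacy is one minus the "hazard ratio estimated from a discrete time proportional hazards regression model with an indicator variable representing treatment arm".

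**The concern.** Section 13.4 allocates participants 1:1 at random, so any baseline difference between arms arose by chance. How much a covariate deserves a place in the adjusted model depends on how strongly it predicts HIV acquisition. Whether it happened to differ between arms says nothing about that. A rule that looks only at imbalance lets in variables with no relation to HIV risk and leaves out strong risk factors that happened to balance. No section makes injecting frequency or needle sharing a fixed covariate, although Section 7 describes the target as parenteral infection.

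There is a second, smaller gap. Sections 13.10 and 14.2 speak of baseline differences, but 13.9 does not limit its behavioral variables to baseline values. The reference to randomization there suggests baseline values are meant. On-trial injecting and sharing are secondary endpoints in 7.2, however, and adjusting the treatment effect for them would be a different analysis. The text should rule it out.

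At stake is whether the adjusted efficacy estimate, in the final report and before the DSMB, comes from a model that could have been written down in advance.

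**Working it through.** **Inputs from the protocol.** 2,400 participants (Section 2); 1:1 permuted blocks (13.4); 40 endpoints, 67% efficacy, a 10% threshold and one-sided alpha 0.025 (13.2); boundaries Z 2.669 at 60% of events and 1.981 at the end (13.10).

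**Assumptions.** The number of candidate variables, their independence, and a 5% imbalance screen. The protocol states none of these. The sentence in 13.7 that reads "A significance level alpha=0.05 will be used to perform significance testing and construct confidence intervals" is general and is not tied to judging imbalance.

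**Step 1: the plan's own figures.** Given 40 endpoints, the tenofovir share is 0.9/1.9 = 0.474 at 10% efficacy and 0.33/1.33 = 0.248 at 67% efficacy. An exact one-sided 0.025 binomial test rejects at 12 or fewer tenofovir endpoints. Its power at 67% efficacy is 82.8%, against 82% in Table 4. O'Brien-Fleming-type spending at 60% information gives Z 2.669 and 1.981, with overall one-sided error 0.0250, as stated. No covariate enters either calculation, so the imbalance rule cannot change them.

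**Step 2: how often the rule would act.** With k independent variables screened at 5%, the expected number flagged is 0.05k and P(at least one) = 1 − 0.95^k.

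| k | Expected flagged | P(at least one) |
|---|---|---|
| 5 | 0.25 | 23% |
| 10 | 0.50 | 40% |
| 15 | 0.75 | 54% |
| 20 | 1.00 | 64% |
| 30 | 1.50 | 79% |

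**Step 3: what it does to the estimate.** The simulation used 2,400 participants, about 40 endpoints and 15 independent binary baseline variables (30% prevalence). One variable was a true risk factor with hazard ratio 2 or 4. There were 4,000 trials under no effect and 2,500 at 67% efficacy.

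| | Unadjusted | Risk factor prespecified | Chosen by imbalance |
|---|---|---|---|
| One-sided error, risk factor HR 2 | 2.5% | 2.4% | 2.3% |
| One-sided error, risk factor HR 4 | 2.0% | 1.7% | 1.9% |
| Power against 10%, risk factor HR 2 | 81.3% | 81.3% | 81.5% |
| Power against 10%, risk factor HR 4 | 84.4% | 84.2% | 84.1% |

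The simulation error on a rate near 2.5% is √(0.025 × 0.975 / 4,000) = 0.25 percentage points, so the columns do not differ materially. At least one variable was flagged in 52% to 55% of trials. In those trials the log hazard ratio moved from its unadjusted value by a median of about 0.013 (e^0.013 = 1.013, about 1%). The 95th percentile was 0.044 to 0.072, against a standard error of 0.33 to 0.40.

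**Step 4: a second set of assumptions.** With 12 binary factors, four of them with hazard ratio 2, and 3,000 trials under no effect, 45.1% of trials flagged at least one variable (formula: 1 − 0.95^12 = 46%). One-sided rejection was 2.07% unadjusted, 1.90% chosen by imbalance and 1.93% with a fixed list. The log hazard ratio moved by more than 0.05 in 4.1% of trials.

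Neither simulation forces age and gender into the imbalance-chosen model, so both describe only the conditional part of the 13.9 rule.

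**The case against.** The strongest reply is that nothing decisive depends on the rule. The test is a log-rank statistic, the boundaries in 13.10 are for that statistic, and the efficacy estimate comes from a model with treatment alone. The simulations show no error inflation, and no gain in power from prespecifying the risk factor. All of this stands, and it makes the point a minor one.

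A second reply is that the section is a summary and that the SAP, not available here, may give the detail. That holds for the measure of imbalance, a cut-off and a limit on the number of covariates, and their absence is not held against the protocol. It does not cover the criterion itself, which the protocol states as a rule. A SAP that followed it would inherit it, and a cut-off would make the rule reproducible without making it right.

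A reader might infer four stronger things that the protocol does not support:

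- **That all adjustment is data-driven.** Age and gender are fixed in 13.9.
- **That the main efficacy result depends on the selection.** It does not, as Step 1 shows.
- **That covariates are picked for their effect on the result.** The stated trigger is the distribution of the covariate, not the outcome, and 13.3 and 13.5 keep analysts and statisticians blinded.
- **That the interim and final models would differ.** Section 8 describes enrollment as reaching 2,400 participants or 24 infections, whichever is first, and the efficacy interim is at about 24. On that reading enrollment is complete or nearly so by the interim, and the baseline comparison would be much the same at both looks. Section 2 mentions only the 2,400, so this is not certain either way.

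**Conclusion.** The point holds as a low-priority improvement. For every covariate other than age and gender, the protocol selects on chance imbalance where it should select on expected association with HIV acquisition, and 13.9 does not say that behavioral variables must be baseline values. The effect is limited to supportive adjusted estimates. Under the assumptions above, the usual shift in the hazard ratio is about 1%, and at the 95th percentile it is at most about a fifth of a standard error. The frequencies of 23% to 79% rest on an assumed 5% screen of 5 to 30 independent variables. They show how readily such a rule would act, and are not a forecast for this trial. The gain from correcting it is an adjusted estimate that is fixed in advance, not more power or tighter error control.

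**What to change.** In 13.7, 13.9, 13.10 and 14.2, replace the imbalance trigger with one prespecified adjusted model containing age, gender, baseline injecting frequency and baseline needle sharing. State that only baseline values are used, and that the same model applies at the interim and final analyses. Keep the baseline table as description only. Section 14.2 must be changed with the others, or the DSMB reports would still follow the old rule.

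The data should already be there: Section 8 and Table 2 place the risk questionnaire at enrollment, and 7.2 lists injecting frequency and needle sharing among the behaviors measured. Hold the list to about four covariate parameters. That leaves 40/4 = 10 endpoints per covariate parameter at the end, but only 24/4 = 6 at the interim, so the interim adjusted estimate should be read with care.

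The cost is wording. No sample size, endpoint count, power figure or boundary changes. The downside is that a chance imbalance in an unlisted variable would only be described, or handled in a sensitivity analysis.

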**13.8 Analysis of safety outcomes**

AEs, SAEs, and abnormal laboratory test results will be compared between the study arms. Factors that may be associated with AEs will be analyzed. AEs will be organized by frequency, severity, and relationship to study agent in each study arm. Rates of AEs among tenofovir and placebo recipients will be compared using chi-squared tests. Longitudinal analysis of AEs will be examined using generalized estimating equation (GEE) logistic regression. The time to adverse event will be examined using Kaplan-Meier plots, log-rank tests, and Cox proportional hazards models to compare the incidence of AEs.

**13.9 Efficacy analysis**

The study hypothesis is that HIV incidence will be lower among participants receiving tenofovir than among participants receiving placebo. A log-rank statistic will be used to test the efficacy of treatment.25 The efficacy of treatment will be estimated as

Efficacy = 1 – *RR*

where *RR* is the hazard ratio estimated from a discrete time proportional hazards regression model with an indicator variable representing treatment arm. Confidence intervals for efficacy can be calculated using the confidence limits for the *RR*.

All analyses will be performed on an intention-to-treat basis. Rates of HIV seroconversion with Poisson 95% exact confidence intervals will be used to summarize the data. Discrete time proportional hazards regression will be applied to adjust the treatment effect for age and gender and for other demographic or behavioral variables, which, despite the randomization, were heterogeneously distributed between the study arms.

**13.10 Interim analysis plan summary**

A safety analysis will be conducted when approximately 200 person-years of participant observation are accrued. Assuming SAE rates among placebo recipients are similar to rates in the AIDSVAX B/E trial (i.e., 7/100 person-years), we calculated power to detect differences in relative rates of SAEs with 200 person-years of follow-up time (100 in each arm) using a 2-tail test at the 0.05 level of significance using methods described elsewhere.26

Table 5. Power to detect differences in relative rates of SAE reports at 200 person-year follow-up.

| Expected Placebo Rate | Expected Tenofovir Rate | Relative Rate | Power |
| --- | --- | --- | --- |
| 7/100 | 14/100 | 2.0 | 32% |
| 7/100 | 17.5/100 | 2.5 | 46% |
| 7/100 | 21/100 | 3.0 | 71% |
| 7/100 | 24.5/100 | 3.5 | 83% |
| 7/100 | 28/100 | 4.0 | 91% |
| 7/100 | 31.5/100 | 4.5 | 95% |
| 7/100 | 35/100 | 5.0 | 97% |

We have 83% power to detect an SAE rate of 24.5 per 100 person-years or higher (RR > 3.5) at the first safety evaluation.

Additional safety analyses will be conducted annually. Efficacy analyses will be conducted when approximately 24 seroconversions have accrued and at the end of the study (40 seroconversions). A group sequential design will be applied to handle multiplicity in analyses. The DSMB will be advised to continue/prematurely stop the trial based on O’Brien-Fleming stopping boundary27 using an alpha-spending function approach where the overall type-1 error rate of 0.025 (1-tail) can be spent in a flexible manner28. As the trial has been designed as an end-point driven trial for a total of 40 seroconversion, we will use direct monitoring to control type-1 error (0.025); using EAST software (EAST v5, Cytel Software, Cambridge MA, 2007) and the alpha spending function as specified. The cut-off points for the 1-tail log-rank Z-test at the interim and final analyses will be:

- First interim analysis (60% of total events): Z > 2.669 or p < 0.003804 (1-tail)
- Final analysis: Z > 1.981 or p < 0.023796 (1-tail)

If the point estimate of efficacy at the interim analysis is <20%, a conditional power futility analysis29 will be carried out. If the conditional power futility analysis shows less than 10% power to demonstrate a lower 95% confidence interval of tenofovir efficacy of >10% given the observed data and using the original trial assumptions of event rates for future observations in the remaining person-years to be accrued, the DSMB will consider recommending trial termination.

The interim analysis report will include a list of AEs, missed visits, drop-outs, adherence information, protocol violations and number, percentage and rates of occurrence of primary and secondary outcomes. Frequencies and crude rates with 95% confidence intervals will be used for data summarization. If necessary, adjustment of sample size will be performed. Multivariable analysis will adjust for baseline differences between study arms.

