**13.2 Effectiveness outcome**

Efficacy analysis is designed to determine if tenofovir efficacy to prevent HIV infection exceeds a threshold level of 10%. A lower threshold of 10% was selected in order to provide a result that can guide public health actions. HIV incidence during the AIDSVAX B/E HIV vaccine trial was 3.4 per 100 person-years. We suspect HIV incidence among IDUs in Bangkok has declined due to HIV prevention activities of BMA drug treatment clinic staff and changes in drug use (i.e., less heroin, more midazolam and methamphetamines)5. In order to ensure that there is sufficient power to achieve the study’s primary objective, to determine if tenofovir prevents HIV infection, we will use an endpoint-driven study design. Based on simulations assuming tenofovir efficacy of 50%, 67%, and 90% and a 1-tail alpha of 0.025, we determined power to provide a result with a lower limit 95% CI > 10% (Table 4).

Table 4. Power to demonstrate tenofovir efficacy with 95% CI >10%

| Estimated Tenofovir Efficacy | Expected Endpoints by Group | | | Power to show tenofovir efficacy with lower limit 95% CI > 10% |
| --- | --- | --- | --- | --- |
| Tenofovir | Placebo | Total |
| 50% | 12 | 24 | 36 | 37% |
| 67% | 9 | 27 | 78% |
| 90% | 3 | 33 | 99% |
| 50% | 13 | 27 | 40 | 49% |
| 67% | 10 | 30 | 82% |
| 90% | 4 | 36 | 99% |
| 50% | 14 | 30 | 44 | 54% |
| 67% | 11 | 33 | 86% |
| 90% | 4 | 40 | >99% |

If tenofovir efficacy is 67%, we have 82% power to demonstrate at least 10% tenofovir efficacy with 40 endpoints. A human post-exposure prophylaxis study suggests tenofovir efficacy to prevent HIV infection will exceed 67%.8

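### The efficacy design, power table and futility rule require efficacy above 10%, but the stated final test is against no effect, and nothing says which decides success

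*Protocol*

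**What the plan says.** Section 13.2 sets the target: "Efficacy analysis is designed to determine if tenofovir efficacy to prevent HIV infection exceeds a threshold level of 10" per cent. It gives a reason: "A lower threshold of 10% was selected in order to provide a result that can guide public health actions". The power simulations used the same criterion with "a 1-tail alpha of 0.025, we determined power to provide a result with a lower limit 95% CI > 10" per cent, and the summary of Table 4 reads "If tenofovir efficacy is 67%, we have 82% power to demonstrate at least 10% tenofovir efficacy with 40 endpoints".

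Section 13.9 frames the hypothesis only as lower incidence on tenofovir than on placebo, and says "A log-rank statistic will be used to test the efficacy of treatment". Section 13.10 plans efficacy looks at about 24 and at 40 seroconversions with O'Brien-Fleming-type alpha spending (0.025, one-sided), and states: "The cut-off points for the 1-tail log-rank Z-test at the interim and final analyses will be" Z > 2.669 at the interim and Z > 1.981 at the end. No shifted null is mentioned.

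The futility paragraph of 13.10 goes back to the 13.2 criterion. If estimated efficacy is under 20% at the interim, the DSMB considers termination when there is "less than 10% power to demonstrate a lower 95% confidence interval of tenofovir efficacy of >10" per cent.

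**The concern.** Unless a shift is stated, a log-rank Z tests a hazard ratio (HR) of 1, that is, efficacy of 0%. A lower 95% limit above 10% is a test of HR 0.90. These are different hypotheses with different critical results. If the protocol names both and ranks neither, a result between the two can be called a success or a failure after the data are seen. Three further things depend on the choice: whether the printed power describes the test that will be run, which null the alpha spending protects, and whether futility is judged against the same target as final success.

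**Working it through.** **Inputs.** 1:1 allocation (13.4); looks at 24 and 40 endpoints, cut-offs 2.669 and 1.981 (13.10); 10% threshold and efficacies of 50% and 67% (13.2, Table 4). Assumption: equal person-time per arm. Given the total D, tenofovir endpoints X are then Binomial(D, p) with p = (1 − VE)/(2 − VE), where VE is true efficacy. This gives p = 0.500, 0.474, 0.333 and 0.248 at VE = 0, 10%, 50% and 67%.

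**1. The plan's own figures.** Lan-DeMets O'Brien-Fleming-type spending at information 0.6, one-sided 0.025, gives 2.669 and 1.981, as printed. For power at 40 endpoints and VE 67%:
- 10% rule, success at X ≤ 12: P = 82.8%, matching the stated 82%.
- Log-rank rule, success at X ≤ 13: P = 90.2%, which does not match.

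The binomial does not reproduce every cell of Table 4. At VE 50% and 40 endpoints the table has 49%, against 39.7% (10% rule) and 53.0% (log-rank). The table is described as simulated, and its own column heading assigns it to the 10% criterion.

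**2. Splits at 40 endpoints.** Log-rank Z ≈ (placebo − tenofovir)/√40. Upper limit for HR = exp[log(x/(40 − x)) + 1.96·√(1/x + 1/(40 − x))]; the lower efficacy limit is 1 minus this.

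| Tenofovir v placebo | Efficacy | Log-rank Z | Lower 95% limit | Z > 1.981? | Limit > 10%? |
|---|---|---|---|---|---|
| 12 v 28 | 57.1% | 2.53 | 15.7% | yes | yes |
| 13 v 27 | 51.9% | 2.21 | 6.7% | yes | no |
| 14 v 26 | 46.2% | 1.90 | −3.1% | no | no |

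For 13 v 27: log(13/27) = −0.731 and SE = √(1/13 + 1/27) = 0.338, so the upper HR limit is exp(−0.731 + 0.662) = 0.933. The exact lower limit is 3.4%, with the same conclusion. Table 4 itself expects 13 v 27 at 50% efficacy.

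**3. Probability of that split.** P(X = 13) at 40 endpoints is 13.3% at VE 50%, 7.4% at VE 67% and 2.2% at VE 10%.

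**4. Two-look behaviour.** Score form: Z = (D·p0 − x)/√(D·p0·(1 − p0)), with p0 = 0.5 for HR 1 and 0.9/1.9 = 0.474 for HR 0.90. With the printed cut-offs, success is at ≤ 5 of 24 or ≤ 13 of 40 for HR 1, and at ≤ 4 of 24 or ≤ 12 of 40 for HR 0.90.

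| True efficacy | Log-rank rule (HR 1) | 10% rule (HR 0.90) |
|---|---|---|
| 0% | 2.0% | 0.9% |
| 10% | 4.3% | 2.0% |
| 50% | 53.4% | 39.9% |
| 67% | 90.3% | 82.9% |

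**5. Futility.** Take 11 v 13 at the interim. Efficacy is 1 − 11/13 = 15.4%, so the under-20% trigger applies. Sixteen endpoints remain; taking 67% as the design efficacy, p = 0.248.
- 10% rule: needs at most 12 − 11 = 1 more tenofovir endpoint, P = 6.6%.
- Log-rank boundary: needs at most 13 − 11 = 2 more, P = 20.2%.

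The written rule would put termination before the DSMB (6.6% < 10%), although the final boundary as printed is still reachable with 20% probability.

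**The case against.** The strongest reply is that the protocol has one hypothesis (13.9), one test and one set of cut-offs (13.10), and that 13.2 only explains the sizing. Sizing on a stricter criterion than the test is conservative, and the trial is not short of power on either reading. That last part stands. But 13.2 describes what the efficacy analysis is designed to determine, gives a public-health reason for the threshold, and has its criterion reused in the futility rule. It reads as more than a sizing device.

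The cut-offs do not depend on the null, so they could serve a log-rank test centred at HR 0.90. That is true, but no such centring is stated and 13.9 points the other way. Section 14.2 leaves stopping rules to a data safety monitoring plan that is not at hand. It might clarify the matter, but it does not cure the protocol's own text.

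The futility rule is advisory and cannot raise the type I error, and a stricter futility target can be deliberate. Both points stand. What remains is that the plan does not say so.

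Three stronger readings are tempting and not supported:
- A reader might infer that type I error is uncontrolled. For efficacy of 0 it is controlled, at 2.0%. The 4.3% is an error rate only if efficacy of 10% or less is the null.
- A reader might infer the same conflict at the interim. The smallest margin that crosses 2.669 is 5 v 19, whose plain lower 95% limit is 29.5%, well above 10%. A difference arises only if the 10% null is held to the interim cut-off (Z = 2.60), which the protocol does not say.
- A reader might object that a 95% limit uses 1.96 and the final boundary 1.981. At 40 endpoints no split falls between them on the 10% criterion: 12 v 28 gives Z = 2.20 against HR 0.90, and 13 v 27 gives 1.88.

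**Conclusion.** The point holds as an unresolved contradiction about success at the final analysis. One split out of 40 endpoints (13 v 27) passes the log-rank rule and fails the 10% rule, with probability about 13% at true efficacy 50% and about 7% at 67%. The printed 82% power describes the 10% rule, not the printed log-rank test, which has about 90%. The boundaries protect the null of no effect but allow 4.3% success at exactly 10% efficacy. The futility rule can judge the trial against a target that the stated final boundary does not use (7% v 20% conditional power at 11 v 13).

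These figures rest on equal person-time per arm, exactly 24 and 40 endpoints, and the event-count approximation to the log-rank Z. Unequal follow-up would move them slightly but would not remove the contradiction.

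**What to change.** Name one primary success criterion in 13.2, 13.9 and 13.10. Either choice is coherent.

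(a) Apply the existing 2.669 and 1.981 cut-offs to the null HR ≥ 0.90 at both looks, and keep the log-rank test of HR = 1 as supportive. The 82% power and the futility rule stay as they are. The cost is a slightly harder interim boundary: 4 v 20 instead of 5 v 19.

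(b) Keep the log-rank test of HR = 1 as the only success rule. State that efficacy above 10% is a sizing and public-health benchmark, restate Table 4 power for the test actually used (about 90% at 67% efficacy by the calculation here, to be confirmed by the sponsor's simulation), and align the futility criterion with the final boundary. The cost is that success no longer shows that efficacy exceeds 10%.

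Both are changes of wording, with power recalculated under (b). Neither needs more participants or endpoints. The choice should be made before any unblinded efficacy data are seen.
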